## Abstract

**Background:**

Prostate cancer exhibits a very diverse behaviour, with some patients dying from the disease and others never needing treatment. Active surveillance (AS) consists of periodic PSA assessment (prostate-specific antigen), DRE (digital rectal examination) and periodic prostate biopsies. According to the main guidelines, AS is the preferred strategy for low-risk patients, to avoid or delay definitive treatment. However, concerns remain regarding its applicability in certain patient subgroups, such as African American men, who were underrepresented in the main cohorts. Brazil has a very racially diverse population, with 56.1% self-reporting as brown or black. The aim of this study is to evaluate and validate the AS strategy in low-risk prostate cancer patients following an AS protocol in the Brazilian public health system.

**Methods:**

This is a multicentre AS prospective cohort study that will include 200 patients from all regions of Brazil in the public health system. Patients with prostate adenocarcinoma and low-risk criteria, defined as clinical staging T1–T2a, Gleason score ≤ 6, and PSA < 10 ng/ml, will be enrolled. Archival prostate cancer tissue will be centrally reviewed. Patients enrolled in the study will follow the AS strategy, which involves PSA and physical examination every 6 months as well as multiparametric MRI (mpMRI) every two years and prostate biopsy at month 12 and then every two years. The primary objective is to evaluate the reclassification rate at 12 months, and secondary objectives include determining the treatment-free survival rate, metastasis-free survival, and specific and overall survival. Exploratory objectives include the evaluation of quality of life and anxiety, the impact of PTEN loss and the economic impact of AS on the Brazilian public health system.

**Discussion:**

This is the first Brazilian prospective study of patients with low-risk prostate cancer under AS. To our knowledge, this is one of the largest AS study cohort with a majority of nonwhite patients. We believe that this study is an opportunity to better understand the outcomes of AS in populations underrepresented in studies. Based on these data, an AS national clinical guideline will be developed, which may have a beneficial impact on the quality of life of patients and on public health.

**Trial registration:**

Clinicaltrials registration is NCT05343936.

**Supplementary Information:**

The online version contains supplementary material available at 10.1186/s12894-023-01380-w.

## Background

Prostate cancer is the most common cancer in men. The Instituto Nacional de Câncer (INCA) estimated 65,840 new cases of prostate cancer in Brazil for each year of the 2020–2022 triennium, which represents 29.2% of new cases of cancer in men in Brazil [1].

Prostate cancer has a very diverse behaviour, with some patients dying from the disease and others never needing treatment. PSA (prostate-specific antigen), digital rectal examination (DRE) and Gleason score are used to classify patients into different risk groups, which helps in treatment decisions. Low-risk prostate cancer is defined as clinical staging cT1- T2a, Gleason score ≤ 6 on tumour biopsy and PSA less than 10 ng/ml [2].

Historically, localized prostate cancer has been managed with radical treatments such as prostatectomy and radiotherapy. These interventions can result in potentially serious adverse effects, especially urinary incontinence and erectile dysfunction [3, 4]. Active surveillance consists of periodic assessments with PSA, digital rectal examination and periodic prostate biopsies [5]. AS is the preferred strategy for low-risk patients to avoid or delay definitive treatment. Results in cohorts of patients on AS demonstrated that this strategy is safe in low-risk patients and is considered standard of care by the main guidelines [6–11].

Despite progress made in the use of AS as a treatment option for prostate cancer, concerns remain regarding its applicability in certain patient subgroups, such as African American (AA) men, who are known to have worse prostate cancer outcomes [12]. Research has shown that African American men were notably underrepresented in the main cohorts that demonstrated favourable outcomes in low-risk prostate cancer. Furthermore, these men often have less access to treatments than Caucasian American men, which can lead to disparities in outcomes [13]. In Brazil, where the population is composed of a diverse mix of races, 56.1% of individuals self-report as brown or black according to IBGE data [14].

AS clinical outcomes and economic impact have never been evaluated in Brazil or in the Brazilian public health system. Therefore, this study seeks to validate the AS strategy in the Brazilian population by evaluating an AS cohort of patients and demonstrate the viability of the strategy in the public system. Based on these data, an AS national clinical guideline will be proposed, which may have a beneficial impact on the quality of life of patients and on public health expenditures.

### General objective

To evaluate the outcomes in a cohort of patients with low-risk localized prostate cancer followed by an AS protocol in specialized centres in the Brazilian public health system.

### Specific objectives

In patients with low-risk prostate cancer undergoing AS, to evaluate the following:

Pathological reclassification rate at 12 months.Treatment-free survival rate.Prostate cancer-specific mortality and overall mortality.Metastasis-free survival.Quality of life through EPIC-CP and EQ-5D-5 L questionnaires.Anxiety symptoms, using the GAD-7 questionnaire.An economic impact analysis of the AS strategy.The perception of urologists regarding the AS strategy in patients with low-risk localized prostate cancer in the Brazilian public health system.

### Translational analysis

To evaluate whether PTEN loss by immunohistochemistry has an impact on the clinical outcomes of low-risk prostate cancer patients on AS.

## Methods

### Design

The VigiaSUS study is a multicentre, nationwide, prospective cohort study.

### Recruitment

The study will include patients from all 5 regions of Brazil. Centres will be selected based on the high recruitment potential, experience in the treatment of localized prostate cancer and availability of multiparametric MRI. The centres must agree to send biological samples from prostatic biopsies for diagnostic review and agree to use an AS protocol as a guide for monitoring low-risk prostate cancer. The inclusion of patients in all regions of the country will be representative of the national population. All eligible individuals who meet the inclusion criteria to participate in the study will be considered and invited.

### Inclusion criteria

Eligible patients must be between 18 and 78 years old, have a localized prostate adenocarcinoma diagnosis within 12 months of inclusion and have low-risk disease. Diagnostic prostate biopsy must have at least 12 cores and Gleason score below or equal to 6 (3 + 3). Patients must have PSA less than or equal to 10 ng/ml and clinical staging between cT1 and cT2a. Patients must have had a prostate multiparametric MRI or undergo this exam within the first 3 months of the study. Patients must be fit for definitive treatment and have availability of biopsy material for diagnostic review.

### Exclusion criteria

Clinical contraindication to prostatectomy or radiotherapy, previous treatment with radical therapies or hormonal therapy, low probability of 10-year survival and biopsy pathology with intraductal carcinoma or cribriform pattern.

### Study procedures and process for obtaining data

Patients who meet the eligibility criteria will be invited to participate and to sign Informed Consent Form 1 (ICF 1). The first part of the study consists of sending prostate biopsy specimens for pathological review to confirm the low-risk diagnosis.***(***Fig. 1***)*** The archived paraffin blocks and slides from prostate biopsy will be sent through a specialized company. The analysis will be performed by a pathological laboratory, and if the results do not show high-risk upgrading, patients will be invited to participate in the second part of the study, in which follow-up data will be collected after patients consent and sign ICF 2. The AS follow-up will be carried out by the local assistant medical team with the guidance of an AS protocol for surveillance (Supplemental 1). All medical decisions will be at the discretion of the assistant team.

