### Analysis of prostate biopsy samples

A pathological review of the prostate biopsies will be performed to confirm the low-risk diagnosis. This analysis will be performed in a central pathology laboratory by a specialized uro-oncology pathologist through anatomopathological (AP) and immunohistochemistry (IHC) examination. The AP exam is performed through histological slides stained with haematoxylin and eosin. The architectural arrangement, cytological pattern, presence of perineural permeation, and vascular invasion, among other issues, are evaluated.

IHC exam includes biomarkers related to prostate cancer. A panel with three antibodies will be used: racemase (positive in most neoplastic acini), p63 (whose expression is not identified in neoplastic acini due to the loss of the basal layer), high molecular weight cytokeratin (also lost in neoplasms) and other biomarkers related to prostate cancer, such as PTEN (tensin homologous phosphatase), which may be complementary. The biological samples will be stored in the central laboratory until the end of the study, when they will be returned to the participants.

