## Discussion

This is the first Brazilian prospective study of patients with prostate cancer under AS. The study will include centres that are part of the public health system in which many patients are not offered the AS strategy due to insecurity regarding the accuracy of the exams and adherence of patients to monitoring. Data also show that discrepancies in the Gleason score usually occur in approximately 14.7% of biopsy revisions [23]. This study includes a pathological review of all prostate biopsies and a review of mpMRI images. The outcomes of AS will be quantified to assess the applicability of this treatment. The study will also involve evaluating the perception of urologists regarding AS in the public health system and assessing the main problems, which may help health managers plan future improvements.

Brazil is a large country of great diversity and a mixed race population, and this is, to our knowledge, one of the largest AS study cohort with a majority of nonwhite patients. AA men have worse prostate cancer outcomes, which leads to uncertainties in the indication of AS [24]. As large prospective studies have included few AA men, it is generally reported that more prospective observational studies are required before definitive conclusions can be reached [25]. We aim to help understand the clinical outcomes of AS in populations of different races and socioeconomic statuses.

The study has some limitations. Initially, it will have a short follow-up time, but we will seek to extend the duration of the study to obtain long-term outcomes. The Brazilian population is large and involves great diversity between regions, but the study will seek to balance the inclusion of patients. The study will mainly include patients who exclusively use the public health system, but this group represents the majority of the Brazilian population.

A strength of the study is the dissemination of knowledge about AS, a practice considered standard of care in low-risk prostate cancer, which may help to preserve the quality of life of Brazilian men. The data gathered by the study can be used for future investigations in the Brazilian population. Economic impact evaluation can help guide public policies in the country. Important data will be collected on the sociodemographic profile of the population and on the treatment profile currently being applied in the public health system.

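### The entry rule for the follow-up cohort stops only high-risk upgrading on central review, so men who are not low risk can enter and bias the 12-month reclassification rate

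*Protocol article*

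**What the plan says.** All references are to the protocol article.

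- **Definition of low risk.** Background defines it by clinical stage, PSA and a biopsy Gleason score of at most 6. Inclusion criteria require low-risk disease and "Gleason score below or equal to 6" on the diagnostic biopsy. They do not say whether the local or the central reading decides.
- **Exclusions on pathology.** Exclusion criteria list "biopsy pathology with intraductal carcinoma or cribriform pattern".
- **Purpose of the central review.** Study procedures describe the first part of the study as "sending prostate biopsy specimens for pathological review to confirm the low-risk diagnosis". Analysis of prostate biopsy samples repeats it: "A pathological review of the prostate biopsies will be performed to confirm the low-risk diagnosis".
- **Order of steps.** In Study procedures, men who already meet eligibility sign the first consent form, and the specimens then go for review.
- **Rule for going on to follow-up.** Study procedures then state: "if the results do not show high-risk upgrading, patients will be invited to participate in the second part of the study".
- **Primary outcome.** Outcomes names the biopsy reclassification rate at 12 months. Sampling and sample size plans on 24%, an acceptable difference of 10%, a 5% significance level and 200 patients, for power above 80%.
- **Frequency of grading disagreement.** Discussion notes that "discrepancies in the Gleason score usually occur in approximately 14.7% of biopsy revisions".

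**The concern.** Confirming low risk and finding no high-risk upgrading are different tests. A central Gleason 7 fails the first by the article's own definition. It fails the second only if the undefined term happens to cover it. Eligibility is judged before the review, and no visible text applies it again to the central reading. The entry rule also does not restate the intraductal and cribriform exclusion for that reading.

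This matters because the primary outcome is departure from low risk by month 12. A man above Gleason 6 on the baseline central reading has already departed. If the event is any grade above 6, or is counted from the local grade, he can count as reclassified with no change in his disease. If the event is counted from the central baseline, he stays in the denominator without being at risk of the transition under study. Either way, the rate partly reflects baseline misgrading rather than the course of low-risk disease under surveillance. The article intends to base a national guideline on these data.

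**Working it through.** **1. The plan's own figure.** Inputs: p0 = 24%, a difference of 10 percentage points, alpha 5% (taken as two-sided), n = 200. One-sample test of a proportion, normal approximation:

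power = Φ{ [ |p1 − p0|·√n − 1.96·√(p0(1 − p0)) ] / √(p1(1 − p1)) }

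- p1 = 34%: (1.414 − 0.837)/0.474 = 1.218, so power is 88.9% (exact binomial 86.9%).
- p1 = 14%: (1.414 − 0.837)/0.347 = 1.663, so power is 95.2% (exact binomial 93.3%).

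Both agree with the stated power above 80%. The sample size is not in question here.

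**2. The entry rule against the criteria.**

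| Central reading | Low risk as defined in Background? | Stopped by the entry rule as written? |
|---|---|---|
| Gleason 6 or less | Yes on grade | No |
| Gleason 7 | No | Only if the undefined term covers it |
| Gleason 6 or less with intraductal or cribriform pattern | Yes on grade, but meets a listed exclusion | Not by this rule; only by the exclusion, if it applies to the central reading |

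**3. Size of the effect.** Let f be the share of the cohort already above Gleason 6 on central review, and q their chance of being counted as reclassified at 12 months. Both are assumptions. With 24% in the remaining men:

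observed rate = f·q + (1 − f)·0.24, so shift = f·(q − 0.24)

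| f | q = 0.24 | q = 0.5 | q = 1 |
|---|---|---|---|
| 5% (10 men) | 24.0% | 25.3% | 27.8% |
| 10% (20 men) | 24.0% | 26.6% | 31.6% |
| 14.7% (about 29 men) | 24.0% | 27.8% | 35.2% |

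For example, with f = 14.7% and q = 1: 0.147 + 0.853 × 0.24 = 0.352.

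The value 14.7% is an upper bound. It is the article's figure for Gleason discrepancies of any direction and size, so it may include downgrades and also upgrades that the rule does stop.

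**4. Against the 10-point acceptable difference.** At q = 1 the shift passes 10 points only when f exceeds 0.10/0.76 = 13.2%. At f = 14.7% it does so only when q exceeds 0.24 + 0.10/0.147 = 0.92.

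**5. The other direction.** If the event is counted from the central baseline, q could lie below 0.24. In the limit q = 0 the rate falls to 0.95 × 24% = 22.8%, 0.90 × 24% = 21.6% and 0.853 × 24% = 20.5% for the three values of f.

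**6. Consequence for a comparison with 24%.** An exact upper-tail test at nominal 2.5% needs 61 or more events in 200 (actual level 2.1%). If confirmed men truly have 24% and q = 1, the chance of declaring an excess is 22% at f = 5%, 66% at f = 10% and 93% at f = 14.7%. At q = 0.5 it is 6%, 12% and 22%.

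**The case against.** **Loose wording.** The strongest reply is that high-risk upgrading is shorthand for any move to a higher risk group. The same paragraph says that the review is meant to confirm low risk, and no sentence says that a central Gleason 7 is accepted. Fig. 1, cited at exactly this step, and Supplemental 1, which sets out the surveillance protocol and its inclusion criteria, are not shown and may settle the matter. This stands as a limit: the text shows what the rule permits, not that such men were enrolled. It does not remove the conflict, because the rule is stated and differs from its stated purpose.

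**Intraductal and cribriform pattern.** The exclusion is not restricted to the local reading, so it may well apply to the central one. This largely stands. The entry rule's silence here is a secondary gap.

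**Direction.** A reader might infer that the primary rate is certainly inflated. The article does not support that. It gives neither the grade that counts as reclassification nor the reference reading, and the shift is zero when q = 0.24.

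**Size.** A reader might also take 14.7% as the expected share of upgraded men. The article gives no direction for those discrepancies, and q = 1 is the worst case.

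**Comparability with 24%.** One might conclude that the result could not be compared with the planning rate. That rate comes from a cited cohort whose baseline grading the article does not describe, so comparability cannot be judged either way.

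**Analysis sets.** These are commonly left to the analysis plan, and their absence is not the point. The point is a stated rule that conflicts with the article's own criteria.

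**Conclusion.** The point holds as an internal contradiction with a possible effect on the primary outcome. The rule for entering follow-up is weaker than the review's stated purpose and the low-risk definition, and taken literally it admits men with a central Gleason 7.

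The bias is upward if reclassification means any grade above 6 or is counted from the local grade, and of uncertain direction if it is counted from the central baseline. For q between 0.5 and 1 and f between 5% and 14.7%, the shift is about +1 to +11 points. It exceeds the 10-point acceptable difference only at the extreme. These sizes rest on assumed f and q and on a 24% rate in confirmed men. The sample-size calculation is unaffected.

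**What to change.** 1. Reconcile the wording of the entry rule in Study procedures with the low-risk definition in Background, the Inclusion and Exclusion criteria, and the purpose given under Analysis of prostate biopsy samples. Define high-risk upgrading if the term is kept.
2. Whatever is decided about following the other men, base the primary-outcome denominator on men whose central review confirms Gleason 6 or less without intraductal or cribriform pattern.
3. Use the central baseline grade as the reference for reclassification.
4. Report centrally upgraded men separately, as baseline misclassification.

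The cost is a change of wording and one analysis-set definition. Some enrolled men leave the primary denominator, up to about 29 of 200 at the upper bound. The loss of precision is small: at 24%, the 95% half-width 1.96·√(0.24 × 0.76/n) goes from 5.9 points at n = 200 to 6.4 points at n = 171.

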**Fig. 1 Fig1:**
[figure not shown]
Schematic design of recruitment, approval and start of study collections

### Data collection

Data collection will be carried out individually by the research team of the participating centres. The sociodemographic variables collected will include age, gender, race/skin colour and last month’s family income. Lifetime smoking and alcohol use habits will be recorded. Family history for cancer will be collected, including degree of relationship and age at diagnosis.

Data related to the AS follow-up will be collected, including adherence to the procedures scheduled, data from medical evaluations including symptoms, clinical examination, Charlson Comorbidity Index [15, 16] and total PSA value, PSA density, clinical staging according to the 8th edition of the TNM [17] and data from quality of life questionnaires collected during the study. Multiparametric MRI data and radiological review information from images will be collected, including PI RADS score, number, and localization of suspicious lesions.

Data from prostate biopsies and pathological review will be collected, such as the number and percentage of compromised fragments, location, Gleason score, among others and immunohistochemical markers. Additionally, complications related to monitoring will be recorded, including prostate biopsy complications such as bleeding or infection.

The data collected will be recorded in source documents, such as worksheets and electronic medical records. Then, the data will be entered in the electronic case report form on Research Electronic Data Capture (REDCap). The medical records will be accessed in a restricted way, and confidentiality will be strictly observed by the research team.

### Outcomes

The biopsy pathological reclassification rate as 12 months is the main outcome. Secondary outcomes included the treatment-free survival rate, overall survival rate, cancer-specific mortality rate, metastasis-free survival rate and rate of complications of prostate biopsies.

### Active surveillance protocol

The study AS protocol was designed by the Uro-Oncology Group of the Hospital Moinhos de Vento using the main internationally validated AS protocols as references, such as the Prostate Cancer Research International Active Surveillance (PRIAS) [18]. Our goal with the protocol is to standardize the follow-up of the cohort so that it can serve as a guide for patient management. The protocol describes the inclusion criteria, monitoring schedule and triggers for biopsy and definitive intervention.

### Analysis of prostate biopsy samples

A pathological review of the prostate biopsies will be performed to confirm the low-risk diagnosis. This analysis will be performed in a central pathology laboratory by a specialized uro-oncology pathologist through anatomopathological (AP) and immunohistochemistry (IHC) examination. The AP exam is performed through histological slides stained with haematoxylin and eosin. The architectural arrangement, cytological pattern, presence of perineural permeation, and vascular invasion, among other issues, are evaluated.

IHC exam includes biomarkers related to prostate cancer. A panel with three antibodies will be used: racemase (positive in most neoplastic acini), p63 (whose expression is not identified in neoplastic acini due to the loss of the basal layer), high molecular weight cytokeratin (also lost in neoplasms) and other biomarkers related to prostate cancer, such as PTEN (tensin homologous phosphatase), which may be complementary. The biological samples will be stored in the central laboratory until the end of the study, when they will be returned to the participants.

